### Participants, screening and randomisation

Participants will include any female adult refugee (aged over 18 years) from South Sudan living within study villages in Rhino Camp who: (1) is experiencing psychological distress based on attaining a score of 5 or more on the Kessler 6 (K6; Kessler *et al*. 2010); (2) can understand spoken Juba Arabic (according to self-report). Exclusion criteria will be determined through a structured screening questionnaire administered by trained research assistants, and will include: (1) imminent risk of suicide or other life-threatening risk; (2) observable signs of a severe mental disorder (e.g. psychosis); (3) inability to understand the basic intervention materials (with items 2 and 3 assessed using an observation checklist).

Within each village, households will be randomly selected by spinning a bottle to decide which direction to start in, approaching the first household in that direction and then approaching every fifth house after that. Within households, we will inquire whether there are Juba Arabic-speaking adult women. If more than one woman meets these requirements, we will randomly select one by drawing numbered slips of paper, and screen the woman who drew the slip numbered as one. Potential participants will be screened for eligibility, and recruitment and screening will continue until two SH+ groups (20–25 people per group, or around 40–50 participants in total) have been identified. Assuming that 60% of participants screened will be eligible and willing to participate in the study [conservatively estimated on eligibility rates of 76% in the uncontrolled pilot (Tol *et al*. under 2018*a*)], we estimate needing to screen approximately 1050 individuals. However, screening will be continued until the target sample is achieved. Based on the population statistics ([name], Health Information System Officer, Public Health Section, UNHCR, Geneva) and experiences in preliminary studies (Tol *et al*. 2018*a*, *b*), we estimate that recruiting sufficient participants from each of 14 clusters will be feasible. To ensure participant retention in the study, we aim to keep detailed address information and discuss current location with family members if participants have moved.

After baseline, simple randomisation of villages will be conducted via software by staff at Johns Hopkins University not involved in the study, and they will reveal allocations to the local implementation team who will inform refugee leaders and individual participants which condition their village has been allocated to, in preparation for intervention commencement. Allocation of villages will not be revealed to the independent assessment team until the end of the trial.

### Outcome measures

The primary outcome is psychological distress across time (T1, T2, T3). Secondary outcomes are: self-defined psychosocial concerns, symptoms of depression and PTSD, hazardous alcohol use, feelings of anger, interethnic group relations, psychological flexibility, functional impairment and subjective wellbeing. The primary end-point is the 3 month follow-up (T3). However, we will also examine the effects of the intervention between baseline (T1) and post-treatment (T2). All measures have been systematically translated from English to Juba Arabic according to standard procedures (van Ommeren *et al*. 1999) and piloted. Psychometric properties were found to be suitable in the preliminary studies, and internal consistencies (using Cronbach's *α*s) are reported below in parentheses. Socio-demographic data will be collected through questions A1–A5 of the WHO Disability Assessment Schedule 2.0 (WHODAS; World Health Organisation, 2010). Outcomes will be assessed through one-to-one interviews in participant homes. These will be conducted by an assessment team, comprised of trained research assistants with strong Juba Arabic and English language skills, and an independent assessment team leader. To accommodate low literacy, pictorial flashcards will be used to depict answering options for the outcome measures. These have been used in preliminary studies and are well understood.

#### Primary outcome: psychological distress

We will measure psychological distress using the K6 (Kessler *et al*. 2010) (*α* = 0.64). This is a brief six-item scale of non-specific psychological distress, screening for the presence of serious mental illness. It has been used in the WHO World Mental Health Surveys and validated in many different countries. Scores range from 0 to 24, and in most applications, a score of 13 or above has been interpreted as indicating a probable serious mental illness (Kessler *et al*. 2003), whereas a score of 5 or more is indicative of moderate or severe psychological distress (Prochaska *et al*. 2012). We will use the K6 as both a screener and an outcome measure.

#### Secondary outcomes

We will assess self-defined psychosocial goals using the Psychological Outcome Profiles instrument (PSYCHLOPS; Robinson *et al*. 2004) (*α* = 0.82). This consists of four questions and three domains: problems (two questions), function (one question) and wellbeing (one question). Participants are asked to give free-text responses to the problem and function domains. Responses are scored on a six-point scale producing a maximum score of 18. The pre- and post-therapy versions of PSYCHLOPS consist of the same four questions but the post-therapy version adds an overall evaluation question (determining self-rated outcome ranging from ‘much better’ to ‘much worse’). PSYCHLOPS has been validated in primary care populations across several countries (Czachowski *et al*. 2011; Héðinsson *et al*. 2012).

We will administer the abbreviated six-item version of the PTSD Checklist-Civilian (PCL-C; Lang & Stein, 2005) (*α* = 0.64) to assess PTSD symptoms. The PCL-C scale uses a five-point response scale, to give a total score ranging between 6 and 30 with higher scores indicating higher levels of PTSD symptoms. It has been well validated across cultures.

To assess depression symptoms, we will use the Primary Health Questionnaire nine-item version (PHQ-9; Kroenke *et al*. 2001) (*σ* = 0.85). The PHQ-9 scale uses a four-point response scale, giving a total score between 0 and 27, with higher scores indicating more depression symptoms. The PHQ has been previously used with South Sudanese internally displaced people (Kim *et al*. 2007).

We will assess hazardous alcohol use through two survey questions designed for the purpose of this study, asking how many days in the last week the participant drank alcohol and how many days they became intoxicated. We will use the addition of the number of days for both questions as a continuous variable.

To assess anger, we will use a shortened version of the explosive anger index, which was developed by Silove *et al.* for use in post-conflict Timor-Leste (Silove *et al*. 2017) and with perinatal women (Silove *et al*. 2015). Our shortened version asks two questions to identify whether participants have experienced attacks of explosive anger (presence score). Participants who endorse these items, will be asked further questions about frequency, what triggers attacks and whether attacks are associated with verbal or physical violence (severity score).

To assess ethnic relations, we developed three questions (*α* = 0.87) that ask about frequency of interacting with people from other ethnicities, in terms of greeting and having conversations in public places, and meeting in one's home. Questions have a four-point response format ranging from 0 (never) to 3 (very often). We will sum answers to form a continuous variable ranging between 0 and 9.

We will assess functional impairment using the WHODAS 2.0, a 12-item interview-administered version (World Health Organisation, 2010) (*α* = 0.82). This instrument assesses health and disability across all health conditions, is applicable across cultures, can be used in all adult populations and has been used in Uganda (Nyirenda *et al*. 2013). WHODAS 2.0 covers six domains (cognition, mobility, self-care, getting along, life activities and participation). It assesses difficulties people have across these domains during the last 30 days.

To assess subjective wellbeing, we will administer the WHO-5 Wellbeing Index, a five-item questionnaire measuring current psychological wellbeing and quality of life (Bech *et al*. 2003) (*α* = 0.80). Scores range from 0 to 25. The scale has demonstrated sensitivity to change in wellbeing and is available in numerous languages (Bech *et al*. 2003).

To assess psychological flexibility, we will deliver the Acceptance and Action Questionnaire (AAQ-II; Bond *et al*. 2011) (*α* = 0.82), a seven-item scale, using a seven-point response scale. Scores range from 0 to 49, with higher scores indicating higher psychological flexibility. It has been used in post-conflict settings (Kashdan *et al*. 2009). Psychological flexibility will be included both as a secondary outcome and as a mediator of the primary and other secondary outcomes.

#### Moderators

To assess the level of exposure to different potentially traumatic events, we will administer an adapted 23-item version of the Harvard Trauma Questionnaire Part A (HTQ; Mollica *et al*. 1992) (*α* = 0.71). Respondents are asked whether they have experienced each of the events. For this study, several items were removed and others added based on contextual relevance in consultation with the local research and clinical team, and one item on torture was adapted from the original version of the HTQ. Two items on the HTQ Part A assessing domestic violence and sexual assault were replaced by three adapted items from the WHO Violence Against Women measure (World Health Organisation, 2005) that were perceived to enhance the ability of the scale to capture these experiences.

At T3, a single question will be asked about any potentially stressful or upsetting events participants have experienced during the trial period. Responses will be coded with general categories (e.g. violence, riots, hunger, destruction of home or property). PCAF reports will be used to identify additional community-level events that may affect particular villages.

A measure of attendance at sessions will be collected via session attendance sheets kept by intervention facilitators.

#### Use of services

To assess the use of EUC services by participants in both trial arms, an identifier will be added to the PCAF routine assessment to indicate whether the participant is in the SH+ trial. At the conclusion of the trial period, data will be gathered on access to any PCAF service (i.e. assessments, group support psychotherapy, medication, social work home-visits, counselling or group health talks).

To assess other health service usage, participants will be asked to list any health service they used for any health problem in the past month, including traditional healers. They will then be asked to identify expenditures in the past month on healthcare, through a series of nine questions.

### Enhanced usual care

EUC will be provided to participants in both SH+ villages as well as participants in control villages. We selected EUC as the comparator to avoid possible nocebo effects associated a waitlist condition (Furukawa *et al*. 2014), while providing more substantial support than usual care. It will consist of an individual visit from a Community Psychosocial Assistant (CPA; a trained Village Health Team member who is a South Sudanese refugee), employed on a small facilitation fee. The CPA will be aware of the allocation of the village and will provide information to all participants over one session of approximately 10–15 min held in the participant's home and covering: the effects of psychological distress; simple strategies to manage ‘overthinking’ (such as physical exercise, regular sleep and keeping a regular routine); services available via PCAF and how to access them. The CPAs will be of mixed sex. Other services will not be restricted in any way to participants in either condition, but will be monitored.

The standard PCAF services include assessments, and then based on need and preferences: psycho-education, group and individual psychological interventions, social work home visits, counselling, medication and group health talks. For SH+ participants, the CPA will also provide details of the SH+ programme and schedule of sessions.

### SH+ implementation

The intervention will involve participants attending five weekly workshop sessions (20–25 people) lasting approximately 2 h each, during which pre-recorded audio materials adapted for the local context will be presented, with participants engaging in several experiential exercises and small group discussions. Participants will also be provided with a locally adapted illustrated self-help book to be used outside the sessions. Two facilitators will conduct the workshop, but their involvement will be minimal. Primarily, their role will be to coordinate the group process, for example, stopping and starting the audio, reading discussion exercises and answering basic questions from participants. The content of the intervention is delivered via the pre-recorded materials, with facilitators trained not to provide detailed explanations, in order to ensure fidelity and keep the need for their training and supervision minimal. A written facilitator guide helps facilitators to conduct the course.

SH+ involves teaching participants skills of: present moment awareness and grounding, defusion from and acceptance of difficult thoughts and feelings, identifying valued life directions and taking action in line with those, and compassion for self and others. A brief outline of the five sessions of SH+ is provided in Fig. 2. Skills learned in any session are reinforced in subsequent weeks.

**Fig. 2. fig02:**
[figure not shown]
Outline of SH+ programme.

In Rhino Camp, the audio material will be presented in Juba Arabic – the most common language spoken among South Sudanese. The SH+ book is largely pictorial because of high rates of illiteracy among South Sudanese refugees, but still contains some text. Pilot testing revealed that literate family members may read the book to illiterate course participants between sessions (Tol *et al*. 2018*a*). The book will be offered to participants in either English (a language increasingly understood by young people) or Juba Arabic. Incentives will not be provided for participants to attend SH+ sessions; however, a soda or water, and a biscuit, will be provided to each participant during each SH+ session due to the length of the sessions. Sessions will be held in tent structures erected specifically for this programme, and mobilisation activities will occur prior to each session.

### Facilitator selection, training and supervision

SH+ facilitators have a minimum of completed secondary education, prior experience with psychosocial activities or community mobilisation and reasonable proficiency in both Juba Arabic (spoken) and English language (written and spoken). Four female facilitators from Arua (Uganda) were employed for the duration of the initial uncontrolled pilot study and prior feasibility cRCT. Training for these facilitators comprised a 5-day training prior to the uncontrolled pilot study and a further 4 days of training prior to the feasibility cRCT because of substantial changes to the SH+ package based on the results of the pilot. This training was conducted by a WHO master trainer [name]. The training provided information on psychological distress, taught skills in identifying and managing participant distress and managing group processes, explained the aims and background to the SH+ intervention, and allowed facilitators to experience taking part in the course themselves. PCAF clinical team members also attended this training, to prepare them to supervise the overall conduct of the intervention and contribute to general capacity building. PCAF clinical team members do not use SH+ techniques, audio-recordings or books in routine services, and the general concepts of ACT and SH+ were not covered sufficiently in training to enable them to be used without materials; therefore, contamination of EUC was not considered an issue.

Competency checks were completed during the training and prior to the feasibility cRCT. These comprised of facilitators completing two role-plays each (one of running an SH+ group session and the other supporting a distressed participant), chosen by the WHO master trainer.

After the feasibility cRCT but prior to the current cRCT, a further four female facilitators from the same area will be employed. The training for these facilitators will be provided in two stages of 4 days each. The first stage will be conducted by the previously trained team who gained experience with SH+ during preliminary studies. This stage will mainly involve listening through the audio course and reading the accompanying book, along with initial practice in running groups. The second stage of the training will be provided by the facilitator team leader in conjunction with the WHO master trainer and focus on the skills covered in the pilot training described above. This will be followed by the same competency assessment. This two-stage approach will also build training capacity in the local facilitator team.

A social worker from PCAF will supervise the conduct of SH+ during the cRCT. The clinical supervisor and the facilitator team leader will receive remote support and supervision on an as needed basis (but no more than 1 h per week) from the WHO master trainer.

Protocol adherence will be ensured through group peer-review sessions after each SH+ session. Peer reviews will cover potential difficulties encountered in delivering SH+, feedback on participant or facilitator concerns, and any adverse events (AEs; e.g. injuries on the way to treatment, increase in distress) and serious adverse events (SAEs; e.g. suicide attempts, serious violence). The facilitator team leader will receive supervision from the clinical supervisor weekly or less frequently, with the supervisor also attending some peer-review sessions to provide support. The structure of the SH+ intervention delivery, supervision and training team is illustrated in Fig. 3.

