## Methods

### Design

This study is a two-arm, single-blind, superiority cRCT, to evaluate the effectiveness of the locally adapted SH+ alongside enhanced usual care (EUC) (SH+), compared with EUC alone. It is conducted in a community-based setting with South Sudanese refugee women living in northern Uganda. All villages in the zones of Rhino Camp where preliminary studies of SH+ have not been implemented (*n* = 14) will be included and randomisation will occur at the village level such that half of the villages will be allocated to receive SH+ and EUC and half will receive EUC alone. Outcomes on a range of mental health indicators will be assessed at the individual level at baseline (T1), post-intervention (T2; 6 weeks) and 3-month follow-up (T3; 19 weeks). The Standard Protocol Items: Recommendations for Interventional Trials (SPIRIT) is outlined in Fig. 1, and the checklist is attached as an online Supplementary file.

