### Ethics and trial procedures

Ethical approval has been obtained from the WHO Ethics Review Committee (ERC), the MildMay Uganda Research Ethics Committee and the Uganda Council for Science and Technology. Permission to conduct research and mental health support activities has been provided by the Office of the Prime Minister in Uganda and the United Nations High Commissioner for Refugees in Uganda.

Potentially eligible women identified through the recruitment process described above will be given oral and written information in the local language about participating in the screening process by a research assistant, who will then seek informed consent for screening. For eligible participants, oral and written information about the trial will be provided by research assistants, and participants will be asked to complete a written consent form. For participants who are illiterate, witnessed oral consent and a thumb print will be considered sufficient. Participants will be free to decline to participate or withdraw without any effect on their routine care.

Small non-financial incentives (e.g. a package of soap) will be provided to compensate participants’ for their time in completing outcome assessments. In case participants do not attend a scheduled assessment, three attempts will be made to contact them to schedule a new appointment, via home visits or contacting other members of the community.

All AEs and SAEs will be recorded by the research team and reported to a data safety monitoring board (DSMB) consisting of an external clinical officer, an external social worker, the project coordinator and the independent assessment team leader. This will occur within 24 h for SAEs and as soon as possible for AEs. A representative from the DSMB will review SAEs within 48 h and, in addition, the DSMB will review all AEs at least twice a month. If necessary, appropriate action will be taken with respect to individual participants, or conduct of the trial (such as referral to specialised care, installing extra assessment points for monitoring participants or discontinuation). No interim analyses are planned. The local project coordinator is responsible for ensuring timely follow-up of any SAEs, and will inform the participants and DSMB if any data indicate that the disadvantages of participation may be significantly greater than expected.

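### The only routine adverse-event enquiry described follows SH+ sessions, so adverse-event counts before T2 are not comparable between arms and tend to overstate harm under SH+

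*Protocol article*

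**What the plan says.** **SH+ arm.** Under SH+ implementation: "The intervention will involve participants attending five weekly workshop sessions (20–25 people) lasting approximately 2 h each". Under Facilitator selection, training and supervision: "Protocol adherence will be ensured through group peer-review sessions after each SH+ session". On the content of those meetings: "Peer reviews will cover potential difficulties encountered in delivering SH+, feedback on participant or facilitator concerns, and any adverse events". The same sentence adds serious adverse events (SAEs). Its examples include injury on the way to treatment, increased distress, suicide attempts and serious violence.

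**EUC-only arm.** Under Enhanced usual care, a Community Psychosocial Assistant (CPA) "will provide information to all participants over one session of approximately 10–15 min held in the participant's home". The listed content is the effects of distress, simple coping strategies and the services available. Asking about AEs is not listed. Of care outside the trial, the section says: "Other services will not be restricted in any way to participants in either condition, but will be monitored".

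**Both arms.** Interviews take place at T1, T2 and T3 (Design). Ethics and trial procedures has the research team record all AEs and SAEs and report them to the DSMB. SAEs go within 24 h, and all AEs are reviewed at least twice a month. That section gives no method or occasion of enquiry. It also says that the local project coordinator "will inform the participants and DSMB if any data indicate that the disadvantages of participation may be significantly greater than expected".

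**The concern.** An AE enters the record only if someone on the trial hears of it. In the SH+ arm, facilitators see the women weekly and have AEs on the agenda afterwards. In the EUC-only arm nobody on the trial is scheduled to see the women during that time. The arms are under observation for the same interval but at different intensity.

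This population has high background distress and exposure to violence (Setting), so events of the listed kinds will occur without any effect of SH+. More of them would be heard of in the SH+ arm. A crude table of AEs by arm would then mix a true effect of SH+ with closer observation. The bias runs towards more recorded harm under SH+. The same unevenly gathered stream reaches the DSMB during the intervention period, largely before any T2 data exist.

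**Working it through.** The article gives no AE rate, no capture probability and no harm threshold, so there is no stated figure to reproduce. The check is a count of contacts, followed by an illustration.

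**1. Scheduled trial contacts after allocation, assuming full attendance**

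| Contact | Section | SH+ | EUC only |
|---|---|---|---|
| CPA home visit | Enhanced usual care | 1 | 1 |
| Weekly sessions, each followed by a review covering AEs | SH+ implementation; Facilitator selection, training and supervision | 5 | 0 |
| T2 and T3 interviews | Design | 2 | 2 |
| Total | | 8 | 3 |

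For SH+ women the CPA also gives the session schedule, so the visit comes before the sessions. Between that visit and T2 the count is 5 v 0. T2 is put at 6 weeks under Design and at 7 weeks under Statistics; this does not alter the count.

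**2. Effect of unequal capture on the observed ratio**

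Let the true risk be p in both arms, with capture probability c1 under SH+ and c0 under EUC. Observed risks are p × c1 and p × c0, so the observed ratio is c1/c0 whatever p is. All capture values here are assumptions.

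- 0.9 v 0.9: ratio 1.00
- 0.9 v 0.7: ratio 1.29
- 0.9 v 0.5: ratio 1.80
- 0.9 v 0.3: ratio 3.00

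**3. Recorded counts, with 294 women per arm (Sample size) and assumed p = 0.10**

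- SH+: 294 × 0.10 × 0.9 = 26.5
- EUC: 294 × 0.10 × 0.5 = 14.7

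That is a gap of about 12 recorded events with no true difference.

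**4. Chance that a two-sided 5% test would call this a difference**

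Two-proportion test, clustering ignored: power = Φ[(d − 1.96 × SE0)/SE1].

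- Observed risks 0.09 and 0.05, so d = 0.04 and the pooled risk is 0.07.
- SE0 = √(2 × 0.07 × 0.93/294) = 0.02104
- SE1 = √[(0.09 × 0.91 + 0.05 × 0.95)/294] = 0.02098
- Power = Φ[(0.04 − 0.04125)/0.02098] = Φ(−0.059) = 0.48

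| Capture, SH+ v EUC | p = 5% | p = 10% | p = 20% |
|---|---|---|---|
| 0.9 v 0.7 | 9% | 14% | 26% |
| 0.9 v 0.5 | 26% | 48% | 80% |
| 0.9 v 0.3 | 57% | 87% | >99% |

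With equal capture the figure is the nominal 5%. Allowing for clustering would widen the standard errors and lower these chances, but it would not change the ratios. The article plans no such test; the table only shows how misleading a crude comparison could be.

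**The case against.** The strongest reply is that the article is a condensed account. A full protocol is available on request (Trial status), and standard operating procedures are mentioned (Trial management). The SPIRIT schedule is a figure that is not shown. AE enquiry in EUC villages may be described in any of these. Moreover, the session reviews are presented as an adherence procedure with AEs as one item, whereas the recording rule under Ethics and trial procedures covers both arms. This stands in part: it would be wrong to infer that AEs go unrecorded under EUC. It does not remove the problem, because events found at session reviews add to the SH+ count whatever else is asked of both arms.

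A second reply is that even-handed information already exists, and this also stands in part:

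- At T3 participants are asked one question about stressful or upsetting events during the trial, with violence among the coded categories (Moderators).
- The K6 and PHQ-9 pick up worsening distress in the same way in both arms.
- The post-therapy PSYCHLOPS adds a self-rated overall change.
- Use of PCAF services is collected in both arms.

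However, the T3 item is a single question, asked once and not linked to AE reporting. The scales do not cover injury or self-harm as events. PCAF contact depends on need and preference.

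A reader might go further and infer that the DSMB cannot judge whether SH+ is harmful. The documents do not support that. The DSMB reviews individual SAEs within 48 h and can act on them, and the article names neither an EUC event rate as the reference nor a between-arm AE test. Nor are the arms observed for different lengths of time; only the intensity of contact differs.

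**Conclusion.** The point holds for between-arm AE counts, mainly for non-serious events between allocation and T2. As described, detection is more intensive under SH+, and a crude comparison tends towards apparent excess harm in that arm. This rests on the contact count of 5 v 0, which comes from the text, and on the inference that regular contact with AEs on the agenda uncovers more events than no contact.

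The size is unknown. The ratio of 1.8 follows only from assumed capture of 0.9 v 0.5, and the false-signal chances also depend on an assumed true risk and on ignoring clustering. Review of individual events and the symptom comparisons at T2 and T3 are not affected.

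**What to change.** 1. Have the masked assessors ask every woman in both arms the same AE/SAE question at T2 and at T3, covering the time since the last interview. The T3 stressful-events item can be extended for this and also used at T2. Word it without reference to sessions or to travel to treatment, so that the answer is less likely to reveal allocation.
2. State that any between-arm harm comparison uses only these solicited events and the symptom worsening measured identically in both arms.
3. Tabulate events found at SH+ session reviews separately, as single-arm safety monitoring. Leave the existing SAE reporting route unchanged.

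The cost is one or two questions at interviews already scheduled, and one further table. The downsides are slightly longer interviews, some recall error, and a small risk of unmasking an assessor, for which Blinding and contamination already has a procedure. The answers are retrospective, so they give the DSMB no comparative data while the sessions are running.

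The article reports T3 data collection as in progress, so a T2 question can no longer be added in this trial. Steps 2 and 3 can still be taken with what both arms were asked alike, and the report should say how each AE came to light.
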